**LIST OF ABBREVIATIONS AND RELEVANT DEFINITIONS**

|                |                                                                                                                                                                                                                                                                                                                                                  |
|----------------|--------------------------------------------------------------------------------------------------------------------------------------------------------------------------------------------------------------------------------------------------------------------------------------------------------------------------------------------------|
| ABR     | ABR form, General Assessment and Registration form, is the application form that is required for submission to the accredited Ethics Committee (In Dutch, ABR = Algemene Beoordeling en Registratie)                                                                                                                                      |
| AE      | Adverse Event                                                                                                                                                                                                                                                                                                                             |
| AR      | Adverse Reaction                                                                                                                                                                                                                                                                                                                          |
| CA      | Competent Authority                                                                                                                                                                                                                                                                                                                       |
| CCMO    | Central Committee on Research Involving Human Subjects; in Dutch: Centrale Commissie Mensgebonden Onderzoek                                                                                                                                                                                                                               |
| CV      | Curriculum Vitae                                                                                                                                                                                                                                                                                                                          |
| DSMB    | Data Safety Monitoring Board                                                                                                                                                                                                                                                                                                              |
| EU      | European Union                                                                                                                                                                                                                                                                                                                            |
| EudraCT | European drug regulatory affairs Clinical Trials                                                                                                                                                                                                                                                                                          |
| GCP     | Good Clinical Practice                                                                                                                                                                                                                                                                                                                    |
| IB      | Investigator's Brochure                                                                                                                                                                                                                                                                                                                   |
| IC      | Informed Consent                                                                                                                                                                                                                                                                                                                          |
| IMP     | Investigational Medicinal Product                                                                                                                                                                                                                                                                                                         |
| IMPD    | Investigational Medicinal Product Dossier                                                                                                                                                                                                                                                                                                 |
| METC    | Medical research ethics committee (MREC); in Dutch: medisch ethische toetsing commissie (METC)                                                                                                                                                                                                                                            |
| (S)AE   | (Serious) Adverse Event                                                                                                                                                                                                                                                                                                                   |
| SPC     | Summary of Product Characteristics (in Dutch: officiële productinformatie IB1-tekst)                                                                                                                                                                                                                                                      |
| Sponsor | The sponsor is the party that commissions the organisation or performance of the research, for example a pharmaceutical company, academic hospital, scientific organisation or investigator. A party that provides funding for a study but does not commission it is not regarded as the sponsor, but referred to as a subsidising party. |
| SUSAR   | Suspected Unexpected Serious Adverse Reaction                                                                                                                                                                                                                                                                                             |
| Wbp     | Personal Data Protection Act (in Dutch: Wet Bescherming Persoonsgegevens)                                                                                                                                                                                                                                                                 |
| WMO     | Medical Research Involving Human Subjects Act (in Dutch: Wet Medisch-wetenschappelijk Onderzoek met Mensen)                                                                                                                                                                                                                               |

## SUMMARY

**Rationale:** Medically unexplained physical symptoms (MUPS) are a serious problem in primary care, with a spectrum from mild to moderate or chronic MUPS. The burden of chronic MUPS is substantial for patients, health care professionals and the society. Therefore, early identification of patients with moderate MUPS to prevent chronicity is needed. Recently a new screenings method with acceptable prognostic accuracy was developed using data from the electronic medical record of the general practitioner. Furthermore, we developed a proactive blended and multidisciplinary preventive intervention to reduce complaints of moderate MUPS and to prevent chronicity, called the PARASOL intervention.

**Objective:** The primary objective is to investigate the effectiveness of the PARASOL intervention on impact of symptoms and physical and mental dimensions of quality of life in patients with moderate MUPS compared with usual care.

Secondary objectives are to study:

- What is the influence of the PARASOL intervention on severity of symptoms, general health, physical behaviour, illness perception and self-efficacy in patients with moderate MUPS?
- What is the cost-effectiveness of the PARASOL intervention in patients with moderate MUPS?

**Study design:** Cluster randomized clinical trial

**Study population:** Patients with moderate medically unexplained physical symptoms, aged  $\geq 18$  years.

**Intervention:** The PARASOL intervention will take 12 weeks with 4-5 face to face sessions with the physical therapist and the mental health nurse as well as weekly online modules. The focus of the intervention is on modifiable prognostic risk factors of chronic MUPS, with integration of principles of the modified consequence model, central sensitisation, cognitive behavioural approach and graded activity.

**Main study parameters/endpoints:** The main study parameters are impact of symptoms and quality of life.

**Nature and extent of the burden and risks associated with participation, benefit and group relatedness:** The risks for subjects are expected to be negligible because of the low impact of the PARASOL intervention. The PARASOL intervention has five face-to-face contacts with the physical therapist, four with the mental health nurse and overarching online modules, with content according to the guidelines. Additionally, the burden of the measurements (filling in questionnaires) at baseline and after three and twelve months will take 30-45 minutes. Furthermore, participants have to wear an activity monitor at baseline, after three and twelve months for one week.

## 1. INTRODUCTION AND RATIONALE

Medically unexplained physical symptoms (MUPS) are a serious problem in primary care(1). Common unexplained symptoms in primary care include pain, fatigue, dizziness and general “malaise”(2). In the Dutch multidisciplinary guideline for MUPS and Somatoform Disorders, MUPS are defined as physical complaints that last for at least a few weeks and are not explained by a medical condition after proper medical examination(3,4). Of all complaints that patients present to their general practitioner (GP), 25–50% cannot be medically explained immediately(5). This percentage is also high in other health care settings. In the practice of the physical therapist, neurologist or internist, 40-60% of patient complaints can also not be explained after proper medical examination(6,7). MUPS can be regarded as a continuum with a spectrum from mild unexplained physical symptoms (low incidence, one or two domains, low impact) moderate symptomatology (more frequent, 2 or 3 domains, higher impact) and persisting or chronic MUPS (high impact, more clusters, chronic)(3,8,9). Seventy percent of the patients who consult their GP with a MUPS related diagnosis improve within two weeks (mild MUPS)(10-12). The other 30% of the patients still experience unexplained symptoms after three months (moderate MUPS)(12). The prevalence rate of patients with chronic MUPS in primary care is approximately 2.5%(5,9,12,13). Patients with chronic MUPS can be distinguished in patients with a functional somatic syndrome (FSS; such as fibromyalgia, chronic fatigue syndrome or irritable bowel syndrome) and patients with a somatic symptom disorder according to DSM V(14).

Despite its low prevalence, the burden of chronic MUPS is substantial(5). The impact on patients quality of life and daily functioning is high, with the lowest scores on domains physical functioning, pain, general health, vitality, and social functioning compared with patients with a major depressive disorder, patients with cancer and the general population(15,16). Patients with MUPS have an above average consultation rate(17), and are more subject to diagnostic procedures(10). For GPs, management of MUPS is challenging and often frustrating, due to the mismatch with the expectations of the patient(18). Besides frustration, GPs experience uncertainty and fear of missing a medical diagnosis, which results in overdiagnosis(10). Additionally, GPs do not timely recognize patients with MUPS(19). It takes about two years before MUPS is diagnosed. In those two years patients will see a medical specialist for about eight times, a physical therapist 14 times and a GP 15 times, leading to increased direct health care costs. Finally MUPS are also associated with increased indirect costs (e.g. work and insurance related costs)(17,20). Absenteeism occurs in approximately 39% of the patients with MUPS.

Treating patients with MUPS is complex. Many intervention studies were already conducted, evaluating pharmacological, psychological, exercise therapy and/or a combination of those. In these studies, the majority of the patients had chronic MUPS(21-24). Education about central sensitization, graded activity, cognitive behavioural therapy and relaxation exercises are known effective treatment modalities in patients with chronic MUPS(3,25). Little research is conducted in patients with moderate MUPS with the aim to prevent chronicity. This is partly

due to the fact that patients with moderate MUPS cannot adequately be identified. Early identification of patients with moderate MUPS will decrease the burden for patients, health care professionals and society. Recently, we developed a new screening method (PRESUME) to identify patients with moderate MUPS using data from the electronic medical record of the GP(26). Patients with moderate MUPS can be identified, the PRESUME screening method showed acceptable prognostic accuracy over 5 years follow-up(27). When patients with moderate MUPS can be early identified, those patients can receive a multidisciplinary primary care preventive intervention to reduce complaints of moderate MUPS and prevent chronicity. We developed a multidisciplinary blended primary care intervention (PARASOL), which is delivered in a combination of eHealth and face-to-face care. The expectation is that this blended care will promote self-management. However, the (cost)effectiveness of this PARASOL intervention needs to be established. It is hypothesised that the PARASOL intervention, focused on modifiable prognostic risk factors of chronic MUPS(1,3,27) in which principles of the modified consequence model(28), central sensitisation(25), cognitive behavioural approach(29-31) and graded activity(32-34) are integrated, can reduce impact and severity of symptoms and increase quality of life, general health, physical behaviour, illness perception and self-efficacy in patients with moderate MUPS.

## **2. OBJECTIVES**

Primary Objective:

What is the effectiveness of the PARASOL intervention on impact of symptoms and physical and mental dimensions of quality of life in patients with moderate MUPS compared with usual care?

Secondary Objectives:

1. What is the influence of the PARASOL intervention on severity of symptoms, general health, physical behaviour, illness perception and self-efficacy in patients with moderate MUPS compared with usual care?
2. What is the cost-effectiveness of the PARASOL intervention in patients with moderate MUPS compared with usual care?

## **3. STUDY DESIGN**

The effectiveness of the blended PARASOL intervention will be studied with a cluster randomized clinical trial with a three and twelve months follow-up period within a primary health care setting. Furthermore, cost-effectiveness will also be assessed six and nine months after baseline using a questionnaire that focus on health care use and indirect costs in the past three months.

[figure not shown]

Figure 1 Overview of the study

## 4. STUDY POPULATION

### 4.1 Population (base)

In this study, 248 subjects with moderate MUPS from primary health care centers will be recruited.

### 4.2 Inclusion criteria

Subjects will be selected and identified with the PRESUME screening method (see figure 2).

In order to be eligible to participate in this study, a subject must meet all of the following criteria; the subjects have to:

- be 18 years or older
- not suffering from chronic somatic or psychiatric disease
- have five or more consultations with the GP in the past twelve months of which at least three of those consultations are with one of the 104 ICPC codes suggestive of MUPS (see Appendix 1).

Health care centers in primary care are eligible to participate if all relevant disciplines (general practitioner, physical therapist, mental health nurse) are available and willing to participate.

### 4.3 Exclusion criteria

Eligible subjects will be excluded when the subject has:

- insufficient mastering of the Dutch language
- no access to the internet.

Furthermore, all identified subjects with moderate MUPS using the PRESUME screening method will be screened by their GP. The GP will exclude the subjects if one or more of the following criteria apply:

- received a medical explained diagnosis between identification using the PRESUME method and the time of inclusion.
- complaints with a shorter duration than one month, in which more diagnostic evaluation of the symptoms is needed.
- unable to participate according to the GP, f.i. because of a life threatening condition, a shortened life expectancy, a major life event in the past month or a MUPS targeted multidisciplinary intervention in the past 12 months.
- the diagnostic phase has not been completed, in other words there is no agreement between GP and patient about sufficient diagnostic testing to rule out a physical cause

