## 8. METHODS

### 8.1 Study parameters/endpoints

#### 8.1.1 Main study parameter/endpoint

The primary parameters are adequate relief and quality of life. Adequate relief addresses symptoms improvement with a validated single question, scored on a dichotomous scale ("Over the past week have you had adequate relief of your symptoms?")(45,46). A responder for adequate relief is defined as a subject who will report adequate relief of their symptoms for at least 6 of the 12 weeks between T0 and T1, and for at least 3 of the 6 months between T1 and T2. Otherwise, a subject will be defined as a non-responder. Adequate relief can be seen as a clinically relevant endpoint at which the individual subject is satisfied with treatment(47). Quality of life will be measured with RAND-36 health survey. The RAND-36 is a valid and reliable self-reported questionnaire. The questionnaire consists of eight subscales; physical functioning, social functioning, role-physical or emotional problems, mental health, vitality, bodily pain and general health. A higher score (0-100) indicate a better quality of life(48,49).

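### Eligibility does not require the unexplained symptoms to be present at inclusion, and the relief responder rule ignores the baseline answer, so recovered patients can dilute the contrast

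*Protocol*

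**What the plan says.** Protocol Section 1 grades MUPS from mild to chronic. It describes the middle grade by severity, "moderate symptomatology (more frequent, 2 or 3 domains, higher impact"), and by course: most patients improve within two weeks, and "The other 30% of the patients still experience unexplained symptoms after three months (moderate MUPS").

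Section 4.2 makes this operational through PRESUME. Besides being adult and free of chronic somatic or psychiatric disease, a subject must "have five or more consultations with the GP in the past twelve months", and three or more of these visits must carry a code from the list of 104 in Appendix 1.

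Section 4.3 adds a filter: "all identified subjects with moderate MUPS using the PRESUME screening method will be screened by their GP". The GP removes patients with a new medical diagnosis, those judged unable to take part, those for whom "the diagnostic phase has not been completed, in other words there is no agreement between GP and patient about sufficient diagnostic testing", and those with "complaints with a shorter duration than one month, in which more diagnostic evaluation of the symptoms is needed".

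Section 8.3 later adds recruitment during consultations and by flyer. The criteria listed there are age, five or more consultations in twelve months, symptoms the GP cannot explain, and a completed diagnostic phase.

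On the outcome, Section 8.1.1 states: "A responder for adequate relief is defined as a subject who will report adequate relief of their symptoms" in at least 6 of the 12 weeks up to T1 and at least 3 of 6 months in later follow-up; everyone else is a non-responder. Table 1 schedules the same question at baseline, and 8.1.3 collects duration of complaints at baseline.

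**The concern.** The trial is meant to describe patients whose symptoms persist and might become chronic. The PRESUME criteria look backwards: coded visits anywhere in the last year qualify, however long ago, and nothing listed afterwards asks whether the complaint is still there. The single duration limit is shorter than the persistence that Section 1 attaches to the moderate grade, and it is worded around diagnostic work-up rather than persistence.

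The responder rule then counts weeks and months with relief without regard to where the patient started. Someone with relief at T0 needs no improvement to be a responder. Such patients respond in both arms alike. At stake are the size of the observed difference on one of the two primary parameters, and whether the enrolled population is the one the objective names.

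**Working it through.** **1. Persistence: the sections side by side.**

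| Place | What it requires |
|---|---|
| Section 1 | moderate MUPS: symptoms still present after three months |
| 4.2 | at least 5 visits in 12 months, at least 3 of them coded; no recency or span |
| 4.3 | a one-month limit, tied to a need for more evaluation |
| 8.3, added routes | symptoms the GP cannot explain; no duration limit or code count listed |

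No row requires symptoms at the time of inclusion. The added routes imply a complaint known to the GP; the PRESUME route does not. One month and three months do not agree.

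**2. Tracing one PRESUME patient.** Suppose three coded visits 8 to 11 months ago, two other visits, and full recovery since.

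- 4.2: five visits and three coded visits within 12 months. Passes.
- 4.3: no new diagnosis, able to take part, diagnostic phase closed, complaint not under a month old and under evaluation. Not excluded.
- Baseline relief question: presumably yes, and not used in the rule.
- Responder rule: 12 of 12 weeks (threshold 6) and 6 of 6 months (threshold 3). Responder, in either arm.

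The patient need not be well all the time. With an assumed relief probability of 0.8 on each occasion, and independent answers, the chance of at least 6 of 12 is 0.996 and of at least 3 of 6 is 0.983. The product is about 0.98.

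**3. Size of the dilution.** The protocol gives no figure to reproduce here. Its sample size rests on RAND-36 physical functioning, and it states no expected responder rates and no share of recovered patients. What follows is therefore illustrative.

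Let s be the share who respond equally often in both arms (rate r), and let the other patients respond at p_C (control) and p_I (intervention). Then

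observed difference = [(1 − s)p_I + s·r] − [(1 − s)p_C + s·r] = (1 − s)(p_I − p_C).

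The rate r cancels. With assumed p_C = 30%, p_I = 50% and r = 90%:

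| s | Control | Intervention | Difference | n per arm, 80% power |
|---|---|---|---|---|
| 0 | 30% | 50% | 20 points | 93 |
| 10% | 0.9×30 + 0.1×90 = 36% | 0.9×50 + 0.1×90 = 54% | 18 points | 119 |
| 20% | 42% | 58% | 16 points | 153 |
| 30% | 48% | 62% | 14 points | 198 |

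The last column is for two-sided α = 0.05, before any allowance for clustering or drop-out. Between s = 0 and s = 30% the requirement grows by 198/93 = 2.1. The differences depend only on s and the assumed 20 points; the last column also depends on the assumed rates.

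**The case against.** Much can be said for the plan.

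- **Three months may not be a formal requirement.** Section 1 defines MUPS as lasting at least a few weeks, which fits a one-month limit, and the three-month sentence reports the course seen in cited studies. The trial aims at early identification, so insisting on three months would move it towards later patients. This stands as a reason not to impose three months. It does not remove the need to say which description the target population must meet.
- **The GP screen does more than apply the one-month limit.** A reader might infer that only very recent complaints are screened out. That holds for duration alone; 4.3 has several other exclusions. A five-week complaint on the PRESUME route also still needs five visits, three of them coded, so it is normally a recent complaint on a record of repeated presentation.
- **Recovered patients have little reason to volunteer** for questionnaires, activity monitoring and, in the intervention arm, 8-10 sessions with weekly online work. This is plausible and may keep the share low. The documents neither show nor exclude it.
- **Figure 2, which sets out PRESUME, could not be read** and may hold further criteria. Section 4.2 nevertheless lists those that a subject must meet.

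Three stronger readings are tempting and not supported:

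- **That the comparison is biased.** Natural recovery occurs in both arms and is what the control group is for. Bias would need selection that differs by arm. Recruitment after centre allocation makes that possible, but nothing here demonstrates it.
- **That the planned 10-point RAND-36 difference falls to 9-7 points.** This takes the treatment effect to be zero in everyone with relief at baseline. Relief is not full recovery of function, and RAND-36 has its own baseline measurement.
- **That the primary analysis should be confined to patients without baseline relief.** That answer is subjective, given after centre allocation, with no patient blinding described. The restriction would conflict with the intention-to-treat principle in Section 10 and reduce the sample.

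**Conclusion.** The point holds in a limited form. No listed criterion requires the unexplained symptoms to be present at inclusion; the one-month limit in 4.3 does not match the three-month description in Section 1; and the responder rule in 8.1.1 disregards the baseline relief answer. A recovered patient can enter, mainly through PRESUME, and be a responder in either arm.

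The consequence is lost contrast on adequate relief and a less clearly defined population. The amount is unknown. The fall from 20 to 18-14 points rests on an assumed 10-30% share, an assumed 20-point difference, and equal response of the affected patients in both arms. These matters are fixed in the protocol's eligibility and endpoint sections, so they are worth correcting there.

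**What to change.** 1. **Current symptoms.** For patients still to be enrolled, add to 4.3 a check that the unexplained symptoms are still present, worded and applied identically in both arms, at the existing GP screen or the researcher's call. For the 520 patients whom the GP has already selected (8.3), the call is the practical place. Cost: one question, and somewhat fewer eligible patients in a trial that has already had to add recruitment routes.
2. **Duration.** Reconcile the one-month limit in 4.3 with the three-month description in Section 1, and state which of them the target population is meant to satisfy. State also whether the 4.3 limit applies to the added routes. Cost: text only, unless the reconciliation changes who is eligible.
3. **Analysis.** Keep all enrolled patients in the primary intention-to-treat analysis. Adjust the relief responder analysis for the baseline relief answer. Report the result in patients who answered no at baseline, and results by duration of complaints, as supporting analyses, noting that both items were collected after centre allocation. Cost: no new data, since Table 1 already schedules both.
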